## Discussion

### Study strengths

The study provides the first AI standardized approach to identifying fetal cardiac anomalies from fetal echocardiography (FE) sweeps in the first trimester.

The study aims to overcome the main limitations of the current approaches for automatizing the FE that target only the second-trimester scan and use Deep-Learning (DL) only to diagnose cardiac heart disease (CHD). In this respect, the techniques used for the automatized interpretation of cardiac ultrasound sweeps will range from timely key feature detection. In addition, the Intelligent Decision Support System (IS) will also be statistically validated at each step.

The study will use information retrieved from general practice during standard evaluation. Therefore, there is no need for additional investigation, such as 4D acquisitions for software development or implementation. Also, the 4D STC technique is highly dependent on the sonographer’s experience, the examination settings and involves significant equipment and additional time costs.

### Study limitations

A limited number of ultrasound devices types and techniques used to acquire the ultrasound sweeps may represent an impediment to large-scale implementation of the study results. The imaging of other ultrasound systems than the ones used to complete the study may differ significantly in the color format, and the performance of the software could be lower. We address this issue by using several color and directional power Doppler techniques and different generations of equipment in the study.

According to the study design, we will include in the study normal hearts; thus, the accuracy for detection of CHD cannot be evaluated from these data.

FE is feasible and efficient during the first trimester. Still, the continuous training process is impaired by the lack of specialists or their limited availability. Therefore, in our study design, the sonographer benefits from a second opinion provided by the developed software, which may be very helpful, especially if a more experienced colleague is unavailable. In addition, the software may be implemented on the ultrasound device so that the process could take place during the live examination.

Also, this software may help improve heart scanning skills because the operator will be stimulated to obtain satisfactory images regarding the key-planes of the cardiac sweep.

This study will provide insight into the feasibility of automatization of the 2D-FE. The aim is to provide a more early and accurate prenatal diagnosis of CHD to improve the treatment options for parents: pregnancy termination or birth in a specialized center. This will ultimately improve the couple’s satisfaction regarding the first-trimester anomaly scan performance, infant survival rates, and the quality of life of the newborns.

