#### I. Data set

##### Ultrasound examination

Women recruited to participate in the study will undergo a fetal echocardiogram between 12-13+6 weeks of gestation. Appropriately competent practitioners will perform fetal scans. The ultrasound machines used are General Electrics

Voluson E10, E8 and E6, and Phillips Epiq Elite, with dedicated software for fetal heart assessment, equipped with convex transabdominal probes (frequency: 3-7MHz). Two-dimensional evaluation of each fetal heart includes a cine loop sweep obtained using Doppler or directional power Doppler techniques, from the four-chamber view plane by moving the transducer cranially towards the upper mediastinum, allowing the visualization of the following planes**:** four- chamber view, left and right ventricular outflow tracts, three vessels, and trachea view [37]. The acquisition time will be set for 5 seconds for each sweep. The cine loop sweeps will be stored on the hard drive of the ultrasound machine.

The protocols for the first trimester examinations are presented in Figs. 1 and 2. An apical-oblique lateral or lateral incidence from the right part of the thorax is considered optimal for visualization of the key-planes essential for fetal cardiac evaluation [29, 30]. Therefore, the operator will focus on other segments of fetal anatomy until the fetus reaches the optimal incidence; the angle beam is narrowed, and high-definition zoom is applied until only the thorax becomes visible, occupying approximately 80% of the screen. The operator then turned on the color flow gate, and a minimum of one duplex video file (grayscale and color / directional power Doppler) will be stored in each patient. The cardiac sweep is aimed to contain the key-planes of heart assessment described below and presented in Fig. 1.

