#### II.Data preprocessing

All video files saved from the ultrasound (US) devices and the frames separated by the OB-GYN/Cardio (OBC) department into folders corresponding to the key planes are collected into the cloud. The Data Science / IT department (DSIT) will process the frames for obeying the anonymization regulations. This implies two essential aspects. One is obviously to erase the information that refers to the patients from the frame samples and the video files, as file and folder names. However, before deleting such information, unique strings will be assigned to each patient, such that, when separating the samples into sets for training, validating, and testing the model, all images that belong to the same patient will be placed in only one of the three sets. In the case that some samples from a patient would be placed in the training set and other samples from the same patient would be put in the validation (or test) set, the machine learning model would be biased since these samples would be more similar compared to those coming from different patients. Hence, before the anonymization takes place, unique codes will be generated for each patient in turn, and the code will appear on the names of the files.

Subsequently, the samples of the patients will be split into training, validation, and test sets, keeping the proportions of 60–20%-20%. These approximate proportions need to be kept for each class in turn. As mentioned above, images belonging to the same patient will be placed in the same set, be it training, validation or test. In addition, even if the samples come from a different video file but from the same patient, e.g., if the patient went to a consultation at another date, the samples will be placed in the same folder to avoid biasing the model.

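### Equipment variety is said to address the risk of lower performance on other ultrasound systems, but no planned result can show whether it does

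*Protocol article*

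**What the plan says.** The relevant statements stand in four places in the Protocol article.

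- **Ultrasound examination** lists four models from two manufacturers: "Voluson E10, E8 and E6, and Phillips Epiq Elite". Three of the four belong to one product line.
- **II. Data preprocessing** assigns patients to training, validation and test sets in proportions of 60%, 20% and 20%. The patient is the unit: "all images that belong to the same patient will be placed in only one of the three sets". The only balancing factor is the image class: "These approximate proportions need to be kept for each class in turn". Device and site are not mentioned.
- **Statistical methods** compares architectures by repeated random sub-sampling with a Wilcoxon signed-rank test. It also compares results on videos from experienced and inexperienced operators. There is no comparison by device.
- **Study limitations** says that images from systems outside the study "may differ significantly in the color format, and the performance of the software could be lower". It continues: "We address this issue by using several color and directional power Doppler techniques and different generations of equipment in the study".

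**The concern.** The named risk concerns machines outside the study, while every planned estimate comes from machines inside it. If all study devices feed the training set, good test results describe devices that the model already knows.

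The article's own reasoning points the same way. It keeps each patient's images in one set because images from one patient resemble each other and would bias the evaluation. It also expects images to differ between systems. The same argument therefore applies to devices, but the split does not carry it over. The model is also directly exposed to this risk: color or directional power Doppler is to supply its main features, one preprocessing option keeps only the Doppler part of the image, and color format is the very property expected to differ.

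What is at stake is what the study can say about use beyond its own machines. The article mentions large-scale implementation and possible installation on ultrasound devices. Without a device-level result, a reader cannot judge whether the stated remedy worked.

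**Working it through.** The plan gives no figure on this point, so there is none to reproduce. The check asks whether any planned result could come from a device absent from training.

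**Inputs**
- From the article: 60% of patients in training; four device models; about 300 video files (section V. Sample size calculation).
- Assumed: one video per patient, so N = 300 patients and 0.60 × 300 = 180 in training; a split made without regard to device; device shares, which the article does not give.

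**Step 1. Chance that a device is absent from training.** For a device used in k of 300 patients, the hypergeometric probability is C(300 − k, 180) / C(300, 180).

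| k patients on the device | Share of 300 | Chance of absence from training |
|---|---|---|
| 1 | 0.3% | 40% |
| 2 | 0.7% | 16% |
| 3 | 1% | 6.3% |
| 5 | 1.7% | 1.0% |
| 10 | 3.3% | 0.008% |
| 15 | 5% | below 0.0001% |

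**Step 2. Chance that all four devices are in training.** This is at least 1 minus the sum of the four absence probabilities. With shares of 80/10/7/3% (240, 30, 21 and 9 patients) it is at least 99.98%. With 70/15/10/5%, or with more even shares, it is effectively 100%.

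**Step 3. Could another planned analysis fill the gap?** The repeated sub-sampling redraws sets from the same pool, so Step 1 applies to each draw with a training fraction near 60%. The experienced and inexperienced operator sets are not said to come from other equipment. No external test site is named. If a rarely used device were absent from training by chance, no result by device is described that would show it.

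**Step 4. What a held-out device could deliver.** As an illustration, take a true recall of 90%, one result per patient, and half-width = 1.96 × √(0.9 × 0.1 / n).
- Equal shares, one device held out: n = 300 / 4 = 75, half-width 6.8 points. This leaves 300 − 75 = 225 patients for training and validation, against 180 + 60 = 240 in the main split.
- Equal shares, one seen device within the 20% test set: n = 60 / 4 = 15, half-width 15.2 points.
- A rarely used device (3%) held out: n = 9, half-width 19.6 points, where the normal approximation is itself poor.
- A dominant device (80%) held out: n = 240, half-width 3.8 points, but only 300 − 240 = 60 patients remain for training and validation.

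The 6.8 and 15.2 points describe the precision of two different quantities, recall on an unseen device and recall on a seen one. Neither measures how optimistic the planned test result is.

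**The case against.** The strongest reply is that addressing a limitation does not mean measuring it. Diverse training data is a recognized way to make a model more robust, and it works only if the devices are in the training set, so the split delivers the remedy rather than defeating it. The article discloses the limitation, makes no cross-device claim in its primary outcome, and speaks of feasibility. Further analyses by device could be left to a fuller document. Three of the four models share a product line, so holding out one of those three tests little. Device may also be confounded with site or operator.

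Much of this stands. Varied equipment is a fair partial mitigation, and a held-out study device is only a proxy for an outside system. What remains is that the article describes both its split and its comparisons and states that the issue is addressed, while nothing in that design can show whether it is.

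A reader might also infer more than the document supports:
- **That the plan promises an unseen-device estimate and fails to give it.** It makes no such promise.
- **That a random split is stated to place all four devices in training, validation and test.** The 60/20/20 split is not called random; that word belongs to the model comparison. Presence in training is near certain for any device with more than a few patients, but a rarely used device could be missing from validation or test: 20% of 9 patients is 1.8.
- **That the data for the check are already in hand.** The article does not say that device identity is recorded or survives anonymization; only a patient code is mentioned.

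**Conclusion.** The point holds as a cheap improvement and a correction of wording, not as an error in the split. Equipment variety may reduce the risk that the article names. Because the split and comparisons ignore device, and no result by device is described, the study as described cannot show that it did.

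Under the assumed 300 patients and a split blind to device, any device with 10 or more patients is in training with a probability of at least 99.99%, and all four are with at least 99.98% even at shares of 80/10/7/3%. The conclusion does not depend on these figures, since no analysis on a held-out device appears anywhere in the article. The loss of performance on an unseen system cannot be sized from the document. The half-widths are illustrative only, because neither device shares nor the number of patients is given.

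**What to change.** 1. Record the device model for each video and keep it as a non-identifying label through anonymization.
2. Report recall per class by device on the test set, with the number of patients behind each figure.
3. After the architecture is chosen, retrain it without the second manufacturer's device (Epiq Elite) and test on that device. Repeat for each Voluson model as a secondary check, noting that the other two models of the same line stay in training. State the training size beside each result.
4. Reword the limitations sentence to say that device variety partly mitigates the risk, and that the held-out-device result is a proxy for, not an estimate of, performance on systems outside the study. One further reason for this caution is that the architecture will have been chosen with all devices in view.

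The cost is up to four extra training runs of one architecture (one main, three secondary), one extra label and a few lines of text. No new patients, staff or procedures are needed. The drawbacks are a possibly less favourable figure, wide intervals if a device is rarely used, a much smaller training set if the held-out device is dominant, and possible confounding of device with site or operator. If the runs are not done, the sentence should at least say that performance on unseen devices is not assessed.

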### Reporting of adverse events

Ultrasound in pregnancy is the most commonly used and powerful tool for diagnosing CHD. The general belief is that diagnostic ultrasound (DUS) does not pose any risk to the pregnant patient or her fetus. Ultrasonography is free of ionizing radiation, but during the examination, it is accompanied by energy deposition in the tissue [42], so there is the potential to initiate biological effects [43]. However, we will analyze the stored videos acquired during the standard protocol during our study, and no supplementary evaluation is required. When using color/power Doppler, the mechanical and thermal indices will be kept as low as possible (ALARA principle) according to safety guidelines [44–46].

In case of any adverse event reported by the patient or observed by the obstetrician, the health professional will act accordingly to ensure patient safety.

## Data Availability

The study results will be disseminated at national and international research conferences and as published articles in peer-reviewed journals. Also, the study will be implemented and reported in line with the STROBE statement. All the anonymized collected data will be processed and stored in the www.zenodo.org research depository. Access to the raw data can be obtained from [name], contact details, [contact], [contact].

## Abbreviations

FE: Fetal echocardiography
DSIT: The Data Science / IT department
DL: Deep-learning
CHD: Cardiac heart disease
IS: The Intelligent Decision Support System
4D STIC: Four-dimensional Spatio-temporal image correlation
AI: Artificial Intelligence
2D: Two-dimensional
US: Ultrasound
OBC: OB-GYN/Cardio
DUS: Diagnostic ultrasound
